**Implementation outcomes**						
Reach	Log record^c^	RA/nurse		x	x	Continuous
Adoption	SDSCA/DTSQ	RA/nurse	x	x	x	Binary
Implementation (fidelity)	Checklist	SP		x	x	Continuous
Self-monitoring of glucose	Self-reported	RA/nurse		x	x	Binary
Medication adherence	Self-reported	RA/nurse		x	x	Binary

*DTSQ* Diabetes Treatment Satisfaction Questionnaire, *EHR* electronic health record, *HbA1c* hemoglobin A1c (aka glycated hemoglobin), *RA* research assistant, *SDSCA* Summary of Diabetes Self-Care Activities Assessment, *SP* standardized patient

^a^The average level of blood sugar over the past 2–3 months

^b^Calculated as weight in kilograms divided by height in meters squared

^c^Number of people participating in the program divided by the number of people eligible to be recruited into the program

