### Outcome measures

We will examine both clinical outcomes and implementation outcomes as we hypothesize that the nurse-led continuum of care program will improve both health and the implementation of priority interventions in diabetes. The outcome measure will pertain to the individual participant level. The primary outcome for the diabetes group is the HbA1c level at 12 months from the intervention. The HbA1c level is indicative of the average level of blood glucose over the past 2–3 months [22]. The primary outcome for the prediabetes group is the incidence of diabetes at 12 months from the intervention.

The secondary outcomes are blood pressure, body mass index (BMI) and lipid levels. Also, the secondary outcomes include a series of implementation outcomes in the RE-AIM (reach, effectiveness, adoption, implementation, and maintenance) implementation framework [23–25]. We provide details on those measures in the following (see Table 2 for a summary).

**Table 2 Tab2:** Measures of outcome variables

	Assessment method	Assessor	Baseline	Midline (6 months)	End line (12 months)	Variable

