#### Implementation outcomes

The RE-AIM (Reach, Effectiveness, Adoption, Implementation, and Maintenance) framework will be implemented as follows:
*Reach* will be measured by the number of people participating in the program divided by the number of people eligible to be recruited into the program.*Effectiveness* will be represented by the clinical outcomes.*Adoption* at the patient level will be measured by the proportion of people adherent to the clinical advice in lifestyle and self-care—this will be measured by the self-reported Summary of Diabetes Self-Care Activities (SDSCA) scale [32] at baseline, 6 months and 12 months (the SDSCA measure is a brief self-report questionnaire that includes items assessing general diet, specific diet, exercise, blood-glucose testing, foot care and smoking) and, in addition, the Diabetes Treatment Satisfaction Questionnaire (DTSQ) [33] will be administered at baseline, 6 months and 12 months (the DTSQ is the most commonly used patient-reported outcome in diabetes trials, which reflects the patient’s perception of the treatment)—and at the clinic level will be measured by the proportion of health clinics successfully recruited into the program over the clinics eligible and approached to participate in the program.*Implementation* will examine the fidelity and quality of the program execution per protocol. To check program fidelity, we will select and train standardized patients (SPs) from the program participants with stable conditions—these SPs will serve as the “secret agents” and the sentry to assess program fidelity with a quality checklist through their routine encounters with the clinicians at the DH diabetes clinic and the nurses; the clinicians will be blinded to the status of the SPs; and the development of SPs and the checklist will follow the protocol we have developed in a separate study [34].*Maintenance* will not be assessed for the purpose of this study.

The hospital and program administrative system will collect a range of other information including detailed program costs, health service utilization and incidence of complications and comorbidities. All data will be entered and securely stored in the EHR, a secured online data capturing and management system developed for the study at the DH.

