### Statistical analysis

Data will be analyzed at the individual (patient) level. Statistical analyses will be performed using the intention-to-treat (ITT) approach in the originally assigned groups. Demographic and baseline characteristics for the intervention and control groups will be presented in the form of mean (standard deviation (SD)) or 95% confidence intervals (CIs) for continuous variables and counts (percentages) for categorical variables. ITT analysis will be performed on the final data collected at 12 months.

Generalized estimating equations (GEEs) with clustering by site, an exchangeable correlation matrix and robust variances will be used to assess the program effect adjusting for potential baseline covariates. The model will take account of clustering and will be used to look at the difference between groups for the HbA1c level at 6 and 12 months, respectively. Multiple imputation will be used to account for the missing values assuming they are missing at random. To test for the secondary sensitivity analysis, data will be analyzed without multiple imputation and without baseline covariate adjustment. The difference in the incidence of diabetes between the groups among the individuals with prediabetes will be tested using a GEE. Statistical significance will be assessed at the 5% level and all analyses will be two-sided. All data analyses will be performed using the Stata 15 (StataCorp, TX, USA) statistical software program.

As we expect that the program effect may differ between several subgroups of the program participants, we plan to do secondary analyses of the following three subgroups for the primary (HbA1C) and secondary (incidence of diabetes) outcomes: the subgroups with poor initial glycemic level (HbA1c ≥ 5.7%) (people with poorer glycemic level at baseline may have a stronger desire to change their behavior); the subgroups divided by gender (in Nepal, women tend to be more adherent to clinician guidance); the subgroups of different social economic classes (people in higher socioeconomic class may be more likely to adhere to lifestyle changes); and government versus nongovernment health centers. The secondary analyses will compare the HbA1c level and incidence of diabetes among people with prediabetes among these subgroups at the end of the 12-month intervention using the generalized linear mixed models with a random cluster effect and adjusting for potential confounders.

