Descriptive statistics (i.e., counts, means and proportions) will be calculated to evaluate the reach, effectiveness, adoption and implementation of the program.

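### Table 2 gives self-monitoring of glucose no baseline, although the self-care questionnaire already records glucose testing at baseline, 6 and 12 months

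*Protocol article*

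**What the plan says.** In Table 2, under implementation outcomes, the row "Self-monitoring of glucose" is self-reported, collected by the research assistant or nurse, marked at 6 and 12 months but not at baseline, and typed as binary. The Adoption row of the same table uses the SDSCA and the treatment satisfaction questionnaire, is marked at all three visits, and is also typed as binary.

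The Implementation outcomes section describes the SDSCA as "a brief self-report questionnaire that includes items assessing general diet, specific diet, exercise, blood-glucose testing, foot care and smoking". It schedules the "self-reported Summary of Diabetes Self-Care Activities (SDSCA) scale [32] at baseline, 6 months and 12 months". Patient-level adoption "will be measured by the proportion of people adherent to the clinical advice in lifestyle and self-care". That section does not define the separate self-monitoring row, place it in a RE-AIM dimension, or relate it to the SDSCA testing items.

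The Outcome measures section gives these outcomes secondary status: "the secondary outcomes include a series of implementation outcomes in the RE-AIM" framework. For their analysis, the Statistical analysis section says: "Descriptive statistics (i.e., counts, means and proportions) will be calculated to evaluate the reach, effectiveness, adoption and implementation of the program".

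**The concern.** The outcome that carries the name of the behaviour has a schedule that omits a baseline the trial plans to collect anyway. This matters because a comparison between arms is intended: the Background hypothesizes better implementation outcomes than under usual care.

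Three features of the design make differences at entry plausible:

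- People with pre-existing diabetes are eligible alongside the newly diagnosed, and some may already test their glucose.
- Health centers are randomized before participants are recruited, and nurses are aware of the assignment (Randomization).
- The trained diabetes nurses identify and recruit participants (Data monitoring and quality assurance).

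A difference at entry can therefore arise through recruitment as well as by chance. A bare 12-month proportion per arm would pass it into the result, and the row supplies no baseline value with which to correct it.

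**Working it through.** The plan gives no sample size, power or expected rate for this outcome, so there is no figure to reproduce. The first step sets the two sources side by side.

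| | Self-monitoring row (Table 2) | SDSCA (Table 2 Adoption row; Implementation outcomes) |
|---|---|---|
| Covers glucose testing | yes | yes, among other items |
| Self-reported | yes | yes |
| Baseline | no | yes |
| 6 and 12 months | yes | yes |
| Type in Table 2 | binary | binary |

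The only documented disadvantage of the named outcome is the missing baseline.

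The second step asks what that omission costs in precision if the arms are compared at 12 months.

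- Input: r, the correlation between the baseline and 12-month values of the outcome as analysed. The document gives none. I assume 0.5, with a range of 0.3 to 0.7.
- Formula: adjusting for baseline multiplies the residual variance by about 1 − r². An unadjusted comparison therefore carries about 1 − r² of the information in the adjusted one. This is an approximation that treats the adjustment as linear and ignores the difference between within-site and between-site correlation.
- r = 0.3: 1 − 0.09 = 0.91.
- r = 0.5: 1 − 0.25 = 0.75.
- r = 0.7: 1 − 0.49 = 0.51.

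If the row applies to the 200 participants with diabetes (also an assumption, since the row does not say), the unadjusted comparison is worth about 200 × 0.91 = 182, 200 × 0.75 = 150 or 200 × 0.51 = 102 participants analysed with adjustment.

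The bias from a systematic difference at entry cannot be sized from the document, which gives no rate of testing at entry in either arm.

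**The case against.** The strongest reply is that this is a secondary outcome in a condensed article. The stated analysis of reach, effectiveness, adoption and implementation is descriptive, and how such an item is derived is usually left to the full protocol or analysis plan. That stands as a limit on the weight of the point. The precision figures apply only if the arms are compared with adjustment. The schedule itself, however, is not left open: Table 2 fixes it and leaves baseline blank.

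Several stronger readings are tempting, and the document does not support them:

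- *The behaviour is counted twice.* The two rows are separate, and no score or composite adds them. The overlap is in reporting only.
- *The yes/no format makes the named outcome inferior to the SDSCA.* Adoption is also typed as binary and summarized as a proportion adherent. The document gives no SDSCA response scale, so a loss from dichotomizing cannot be claimed or quantified.
- *A second, redundant question is asked.* The entry says only that the outcome is self-reported, and the SDSCA is self-reported too. The blank baseline cell suggests a separate question but does not establish one.
- *A difference at entry would go unseen.* The SDSCA data would show it. The fault is that the named outcome is not linked to those data.
- *The favourable version could be chosen for reporting.* Each row is a named outcome with its own result, and nothing indicates an intention to choose between them.

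Chance imbalance, moreover, is already reflected in the standard error at follow-up and costs precision only. The concern about bias rests on recruitment after allocation.

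**Conclusion.** The point holds in a limited form. Table 2 fixes a self-monitoring outcome without a baseline, while the SDSCA already records glucose testing at baseline, 6 and 12 months. The two outcomes overlap, and the one named for the behaviour cannot by itself show change or be adjusted for differences at entry.

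Under the assumed correlation of 0.3 to 0.7, the omission leaves about 91% to 51% of the information, or about 75% at 0.5. The argument about differences at entry rests on documented features: recruitment after cluster randomization by nurses who know the assignment, and eligibility of people with pre-existing diabetes. That some of those people already test is plausible but is not stated.

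The medication adherence row also has a blank baseline, but no baseline instrument is described for it, so the point is specific to self-monitoring. It is minor and touches neither primary outcome nor the sample size.

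**What to change.** In Table 2, give the SDSCA blood-glucose testing item as the source of the self-monitoring row and mark baseline, 6 and 12 months. In the Implementation outcomes section, define the outcome from that item and state that this is the self-monitoring result. Present the 12-month comparison between arms adjusted for the baseline value or, if the analysis stays descriptive, show the baseline and 12-month values by arm side by side. If a separate question is intended, say so, explain why it is needed beside the SDSCA item, and collect it at baseline too.

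The cost is one edited table row and a sentence or two of text. The SDSCA data are already planned at all three visits, and the Trial status section says recruitment had not started.

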#### Clinical outcomes

The clinicians from Dhulikhel Hospital outreach centers not otherwise associated with the project will measure HbA1c, lipid profiles, BMI and blood pressure when the participants visit the diabetic clinic at baseline, 6 months and 12 months.

HbA1c will be measured using Boronate affinity chromatography (Axis-Shield; Norway) [26], LDL and HDL using the elimination method (Dialab; Austria) [27], triglyceride using GPO-PAP (Dialab; Austria) [28] and total cholesterol using CHOD-PAP (Dialab; Austria) [29]. For each type of assay, the laboratory has quality control (QC) materials (using commercially available assayed and unassayed control material) from Bio-Rad Laboratories, USA. Each QC is run at least in duplicate. External QC is arranged by internationally recognized reference laboratories that distribute batches of samples of various concentrations for each assay. The laboratory performs the External Quality Assurance Scheme from an unknown assayed sample from the Department of Clinical Biochemistry CMC, Vellore, India for 23 routine parameters, 5 immunological parameters and HbA1c. Additionally, 5% of the blood samples will be obtained in duplicate and sent for testing of all parameters, blinded to the laboratory personnel.

The mean of three measurements of systolic and diastolic blood pressure, using a Microlife automatic blood pressure measuring device, will be adopted for analysis. Hypertension is defined as systolic blood pressure ≥ 140 mmHg or diastolic blood pressure ≥ 90 mmHg or taking antihypertensive medication [30]. Weight will be measured and recorded to the nearest 0.1 kg, without shoes and with minimum clothing, using an Omron Model HBF-400 scale. Height will be measured without shoes using a standard tape measure with participants standing against a wall for measurement, and recorded to the nearest 0.1 cm. The BMI will be calculated as weight in kilograms divided by height in meters squared. Overweight is defined as a BMI of 25 kg/m^2^ or higher and obesity is defined as BMI of 30 kg/m^2^ or higher based on international cutoff points [31].

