The Dhulikhel Hospital (DH) system is a community-oriented, nongovernmental health system with an extensive network of 21 rural community-based outreach centers. The DH system provides a well-suited setting for innovating a continuum of care for people with diabetes. In this trial, we aim to develop and implement a “continuum of care” program with trained nurses as the nucleus. The nurses, along with the community health worker, will coordinate and implement a composite of the DCP-3-recommended individual intervention components for the low-income setting: leading community awareness campaigns; organizing diabetes screening events; linking diabetic patients to comprehensive clinical care (which will have been structured based on standard guidelines); and ensuring treatment adherence and self-management through regular community-based group counseling programs. The primary objective of this study is to examine the effectiveness of this comprehensive intervention in promoting the health of the people with diabetes and prediabetes, and the secondary objective is to examine whether the nurse coordination will promote the implementation of the evidence-based, DCP-3-recommended interventions. We hypothesize that the NUrse-led COntinuum of care for people with Diabetes and prediabetes (NUCOD) program will improve both clinical outcomes as well as implementation outcomes, compared with diabetes usual care in low-income settings.

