### Setting

The study will be conducted in 26 clusters: 9 outreach centers (Bahunepati, Manekharka, Hindi Health, Baluwa, Bolde Phediche, Dapcha, Kartike Deurali, Salambu and Dhunkharka Health Centers) of Dhulikhel Hospital, Kathmandu University Hospital and 17 government health posts located in the adjoining catchment areas purposively selected from the Kavrepalanchowk and Sindhupalchowk districts. The primary stratification variable, as well as the unit (cluster) of randomization and implementation, will be health clinics (outreach centers and health posts (HPs)). There will be 13 clusters per treatment arm (1:1 allocation ratio). Outreach centers are the small medical health facilities that offer basic and emergency care services in remote areas of Nepal. These centers are run by Kathmandu University Hospital. Similarly, health posts are government-run facilities that provide basic health care and preventive medication in remote rural areas of Nepal.

Kavrepalanchowk district located in Province 3 of Nepal consists of 13 municipalities: 6 urban and 7 rural municipalities with a total of 137 wards. The headquarter of this district is Dhulikhel municipality. A total population of 381,937 resides in this district; 62.51% live in the urban municipalities and 37.49% live in the rural municipalities. There is one 15-bed district hospital, 4 primary health care (PHC) centers and 86 HPs in the district [10]. Sindhupalchowk district, also located in Province 3 of Nepal, consists of 12 municipalities: 3 urban and 9 rural municipalities with a total of 103 wards. The headquarter of Sindhupalchowk district is Chautara. A total population of 287,798 resides in this district; 41.42% live in the urban municipalities and 58.58% live in the rural municipalities. There is one 15-bed district hospital, 3 PHC centers and 75 HPs in the district [10]. The maps of Kavrepalanchowk and Sindhupalchowk districts with the distribution of outreach centers and health posts are shown in Figs. 2 and 3.

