### Randomization

The 26 health clinics will be randomized 1:1 into the continuum of care group (intervention) and the usual care group (control), stratified by outreach center and health post. The usual care group includes those who continue managing their diabetes under the direction of their primary care providers, which is the most commonly used method for diabetes management in Nepal. The selection of the usual care group as a comparator is thus justified. A statistician otherwise not involved in the project will perform this group assignment at the cluster level with simple random selection with the R statistical program. Randomization will be done before participant recruitment. Outcome assessors will be blinded to the group assignment, but the nurses and patient participants will be aware of their group assignment. If blinding to the outcome assessor is accidentally broken, they will follow a standard protocol for reassessment of the patients at another time. Any violations of the study protocol will be recorded and reported to the Ethics Committee.

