**Clinical outcomes**						
*Primary outcome*						
Glycemic control (HbA1c)^a^ for diabetes	Blood sample	Biochemist	x	x	x	Continuous
Incidence of diabetes among prediabetes	EHR	RA/nurse		x	x	Binary
*Secondary outcomes*						
Blood pressure	Electronic monitor	RA/nurse	x	X	x	Continuous
Lipid profile	Blood sample	Biochemist	x	X	x	Continuous
Body mass index	EHR^b^	RA/nurse	x	x	x	Continuous

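### The plan promises blinded outcome assessors but lets nurses, whom it declares unblinded, assess several outcomes, and its text and Table 2 disagree on who measures blood pressure and BMI

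*Protocol article*

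**What the plan says.** Three places in the protocol article bear on who assesses outcomes.

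- **Randomization:** "Outcome assessors will be blinded to the group assignment, but the nurses and patient participants will be aware of their group assignment". A safeguard follows: "If blinding to the outcome assessor is accidentally broken, they will follow a standard protocol for reassessment of the patients at another time".
- **Outcome measures, Table 2:** the assessor column reads RA/nurse for most outcomes, for example "Blood pressure Electronic monitor RA/nurse" and, for the primary outcome in prediabetes, "Incidence of diabetes among prediabetes EHR RA/nurse". BMI, the SDSCA/DTSQ row, self-monitoring of glucose and medication adherence carry the same entry.
- **Clinical outcomes text:** "The clinicians from Dhulikhel Hospital outreach centers not otherwise associated with the project will measure HbA1c, lipid profiles, BMI and blood pressure", at the diabetic clinic visits at baseline, 6 months and 12 months.

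The setting matters here. "The study will be conducted in 26 clusters: 9 outreach centers" plus 17 government health posts, and every patient of a center shares its arm (Design). The intervention section describes one trained diabetes nurse per site, 26 in all. Under Table 1, only the intervention arm receives nurse-led counseling and nurse-coordinated follow-up. The DTSQ is described as an instrument "which reflects the patient’s perception of the treatment".

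**The concern.** One sentence blinds the assessors and unblinds the nurses. The outcome table then makes the nurse an allowed assessor. Both cannot hold for the same measurement.

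Three things are at stake. First, a trial report would claim blinded assessment that the plan does not arrange. Second, a patient in the intervention arm may be asked about satisfaction, self-care and adherence by the nurse who runs that patient's group sessions. A control patient has no such counseling relationship, so any wish to please could act more in one arm than in the other, and intention-to-treat analysis, GEE and multiple imputation do not correct for that. Third, the affected rows are not all minor. Incident diabetes is a primary outcome, the Background hypothesizes better implementation outcomes than under usual care, and the Abstract names implementation outcomes in its primary-outcome sentence.

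**Working it through.** The plan gives no figure to reproduce. The check sets the assessor statements side by side.

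| Table 2 row | Method | Assessor in Table 2 | Assessor in Clinical outcomes text |
|---|---|---|---|
| HbA1c | Blood sample | Biochemist | Outreach-center clinician |
| Incident diabetes | EHR | RA/nurse | none named |
| Blood pressure | Electronic monitor | RA/nurse | Outreach-center clinician |
| Lipid profile | Blood sample | Biochemist | Outreach-center clinician |
| BMI | EHR | RA/nurse | Outreach-center clinician |
| Reach | Log record | RA/nurse | none named |
| Adoption (SDSCA/DTSQ) | Questionnaire | RA/nurse | none named |
| Implementation (fidelity) | Checklist | Standardized patient | none named |
| Self-monitoring of glucose | Self-report | RA/nurse | none named |
| Medication adherence | Self-report | RA/nurse | none named |

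1. **Count.** RA/nurse 7, biochemist 2, standardized patient 1; 7 + 2 + 1 = 10. So 7 of 10 rows permit a nurse, including one of the two primary clinical outcomes. Reach is a participation ratio from a log and leaves little to the assessor's judgment, so six rows are of concern.

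2. **Nurse as assessor.** Randomization says nurses know the assignment. The study nurses the article describes are the trained diabetes nurses, one per site, and the intervention section says they carry tablets holding participants' results. Where a nurse assesses, blinding is contradicted by the plan's own words. The reassessment rule does not help, since it covers accidental unblinding and not an assessor who is unblinded by design.

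3. **Research assistant as assessor.** Research assistants obtain consent (Screening and recruitment) and interview at baseline (Baseline assessment). The article neither says that they are blinded nor rules it out. Blinding here is unsecured, but not shown to fail.

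4. **Clinician as assessor.** The text and Table 2 conflict on blood pressure and BMI. For HbA1c and lipids the mismatch (clinician against biochemist) may only separate sampling from assay, and a laboratory value leaves little room for assessor bias. Assignment is by center, so a clinician who works at one of the 9 randomized outreach centers could infer the arm of its patients. Describing the clinicians as outside the project does not expressly exclude this.

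5. **Self-reports.** Participants know their arm. Whoever asks the questions, SDSCA, DTSQ, self-monitoring and adherence cannot be blinded outcomes. The choice of interviewer changes only how much reporting bias is added.

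**The case against.** The strongest reply is that little is shown to go wrong. The table entry is RA/nurse, so a research assistant may do all the work. The clinicians are described as unconnected with the project, which could already exclude staff of trial centers. Blood pressure is the mean of three automatic readings, and incident diabetes is taken from a record. Nurses are trained at all 26 sites, so control patients may be interviewed by a nurse too.

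Much of this stands, and it rules out several stronger readings.

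- A reader might infer that the clinicians know the arm. No sentence says so; it is only possible for those based at a randomized center.
- A reader might infer that the program nurse performs every assessment. Table 2 permits this but does not require it.
- A reader might infer that the type of interviewer differs by arm. The table names the same assessors for both arms. What differs is the nurse's relationship to the patient, because only intervention patients are counseled.
- A reader might combine the 9 trial centers with "an extensive network of 21 rural community-based outreach centers" to get the share of assessors at trial sites. Nothing says that all 21 centers supply assessors.
- A reader might attach an inflated false-positive rate to the self-reported outcomes. That would need an assumed reporting shift and a significance test, while the Statistical analysis section plans only descriptive statistics for the implementation outcomes. The harm to expect is a distorted estimate, not a computable error rate.

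None of this removes the contradiction. A plan that promises blinded assessors cannot also list an assessor it declares unblinded.

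**Conclusion.** The point holds in a limited form. Assessor blinding as stated is contradicted wherever a nurse assesses blood pressure, BMI, SDSCA/DTSQ, self-monitoring, medication adherence or incident diabetes, and it is not secured where a research assistant or an outreach-center clinician does. The text and Table 2 must also be reconciled on who measures blood pressure and BMI.

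By count, 7 of 10 outcome rows permit an unblinded assessor, six of them of concern. The size of any bias cannot be derived from the documents. The self-reported outcomes are the most exposed. Automatic blood pressure readings and weight are less so, and incident diabetes is exposed only as far as the record leaves room for judgment. HbA1c in people with diabetes is a laboratory assay and is not part of the concern.

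The conclusion assumes that the nurse in Table 2 is the site's trained diabetes nurse, the study nurse the article describes. It should be corrected, but it does not undermine the trial's design.

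**What to change.** - **Table 2:** name one assessor per outcome. Delete nurse from the rows for incident diabetes, blood pressure, BMI, SDSCA/DTSQ, self-monitoring and medication adherence. Have an existing research assistant who does not work at that site collect these data, with the nurse absent.
- **Clinical outcomes text:** make it agree with Table 2. If outreach-center clinicians remain assessors, specify that none assesses patients of a trial center where he or she works.
- **Randomization:** state that self-reported outcomes are unblinded, and likewise any outcome whose assessor cannot be kept unaware of the arm. This may include a research assistant who took consent or learned the assignment at recruitment.

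The change uses research assistants and clinicians already in the plan. It costs some travel and scheduling between sites and a less favorable blinding statement. It reduces reporting bias in the self-reports but cannot remove it, because participants know their arm. The Trial status section says recruitment had not begun, so the change could be made before any outcome data existed.
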